### Sample size planning

Our previous RCT [47] on soy showed a 4.2 mmHg net reduction (SD of change 10 mmHg) in SBP after 6-month soy protein and isoflavones supplementation relative to placebo group among 130 pre- and hypertensive postmenopausal women [48]. Assuming a reduction of 5 mmHg of treatment effect on SBP (main effect), 63 subjects per group will yield a power of at least 80 % at 5 % level of significance (for a 2-side t-test). Allowing for 10 % non-compliance or drop out from the study, 69 subjects per group and a total 207 subjects (63 × 3 × 110 %) will be recruited. Similar attrition rates (7.8 % and 7.0 %) have been reported in our previous soy trials [45, 49].

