### Statistical analysis

Relevant parametric and non-parametric tests will be used for testing the differences in the baseline characteristics and outcomes of post treatment among the three study groups. The major approach of analysis will be one way analysis of variance (ANOVA) to compare the change and percentage change of outcomes at 24 weeks among the three groups. Analysis of covariance will also be made to examine if the results are similar after adjusting for potential confounders. The primary analysis will be an intention to treat (ITT) analysis that included all subjects who are randomized. A secondary per protocol analysis will be performed including subjects with good compliance (defined as subjects who consumed ≥ 80 % of provided supplements or with urinary isoflavones level above predefined values for valid users). The non-compliant subjects will be described and compared to the compliant subjects. Dose-dependent effects will be evaluated with the Jonckheere’s trend test. The Bonferroni test will be used for post hoc multiple comparisons among the three groups. The primary outcome variables of 24 h ambulatory BP (mean SBP and mean DBP in all day) will be tested at a significance level of 2.5 % in order to maintain an overall 5 % level. The two important secondary outcomes for assessment of vascular function (%FMD and PWV) will be tested at a significant level of 1.25 %. Exploratory analyses will be used to test each of the tertiary outcomes at the 5 % significance level. Further stratification analysis will be conducted to examine if the effects differed across subgroups such as years since menopause and BMI etc.

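### The fixed 2.5%/2.5% split between 24 h SBP and DBP is valid, but a step-down rule with the same first step would more often show both (about 7–8 points under assumed DBP inputs)

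*Protocol article*

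**What the plan says.** All of the relevant rules are in the Statistical analysis section of the protocol article.

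- Two primary variables: "The primary outcome variables of 24 h ambulatory BP (mean SBP and mean DBP in all day").
- Their level: they "will be tested at a significance level of 2.5 % in order to maintain an overall 5 % level".
- Main test: "one way analysis of variance (ANOVA) to compare the change and percentage change of outcomes at 24 weeks among the three groups".
- A Bonferroni test is named for post hoc comparisons among the three groups, without a numerical level.
- %FMD and PWV have their own level of 1.25%.

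No sentence lets one BP variable be tested at a higher level after the other has succeeded. The Sample size planning section supplies the only numerical inputs: an SBP effect of 5 mmHg, "SD of change 10 mmHg", and "63 subjects per group will yield a power of at least 80 % at 5 % level of significance".

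**The concern.** The article fixes both a decision rule and its purpose, an overall 5%. For two tests, Holm's step-down rule serves that purpose with the same first step and rejects everything that the fixed split rejects. Suppose SBP gives p = 0.01 and DBP gives p = 0.035. The plan as written calls DBP negative. A step-down rule calls both positive, whether its second step is 5% or 4.17%.

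At stake is the second BP variable, which would be DBP if SBP responds more strongly. The study hypothesis speaks of BP in general, so a conclusion on both variables has some value.

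**Working it through.** **Inputs from the article.** SBP effect 5 mmHg; SD of change 10 mmHg; 63 per arm (69 recruited); three equal arms; 2.5% per primary variable.

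**Inputs assumed, because the article gives none.** SD of DBP change 6 mmHg; DBP effects as in the table below; correlation of SBP and DBP changes 0.5–0.7. Absolute change is analysed by one-way ANOVA.

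**1. The plan's own figure.** Two-group power = Φ(δ/(SD·√(2/n)) − z). With δ = 5, SD = 10, n = 63 and two-sided 5%: 5/(10·√(2/63)) = 2.806, and Φ(2.806 − 1.960) = 80.1%. The stated 63 per group is reproduced.

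**2. The split controls what it claims.** 2 × 2.5% = 5% for the two overall tests, whatever their correlation.

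**3. What second-step level is allowed?** Bonferroni pairs within a 2.5% test have a level of 2.5%/3 = 0.83% each (an inference; the article gives no figure). Assume that pairs are examined only after a significant overall test on that variable, and count a false pair as an error.

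- *No group difference on either variable:* an error needs the smaller p ≤ 2.5%, so the risk is at most 2 × 2.5% = 5%.
- *A true difference on one variable only:* at most one of that variable's three pairs can still be null. The risk is at most 0.83% plus the second-step level, so the second step may be 5% − 0.83% = 4.17%.
- *True differences on both:* at most one null pair each, 2 × 0.83% = 1.67%.

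The second case decides the matter. It was simulated with SBP lowered strongly and equally by both doses and no DBP effect:

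| Level for the second variable | Upper bound | Simulated error |
|---|---|---|
| 2.5% (current split) | 2.5 + 0.83 = 3.33% | about 3.2% |
| 4.17% | 4.17 + 0.83 = 5.00% | 4.7–4.8% |
| 5% | 5 + 0.83 = 5.83% | 5.5–5.6% |

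If only the two overall tests are counted, a 5% second step stays within 5%.

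**4. Gain in power.** Simulated three-group F-tests on 2 and 3 × 63 − 3 = 186 degrees of freedom, 200,000 trials per scenario. Ranges are for correlations of 0.5–0.7.

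| Assumed fall, low/high dose (mmHg) | Both shown, current split | Both shown, 5% second step | Gain with 4.17% |
|---|---|---|---|
| SBP 5/5, DBP 3/3 | 61–64% | 71–74% | 7–8 points (to 69–71%) |
| SBP 2.5/5, DBP 1.5/3 | 43–47% | 54–57% | 7–8 points |

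With SBP 5/5 and a weaker DBP effect of 2/2, the chance of showing DBP rises from 36% to 45% with a 5% second step. With 69 per arm the gains in showing both are about 8–11 points (5%) and 7–8 points (4.17%).

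A separate two-group calculation from a bivariate normal (63 per group, both effects 0.5 SD, 5% second step) gives 57.4% to 67.9% at correlation 0.5 and 60.7% to 70.2% at 0.7. These gains of 10.4 and 9.5 points agree with the simulation.

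**5. What does not change.** The first step is still 2.5%, so the chance of at least one primary success is identical.

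**6. What the added DBP successes contain.** Among trials with SBP p below 2.5% and DBP p between 2.5% and 5%, only about 7–11% have any dose-versus-placebo DBP difference significant at 0.83%.

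**The case against.** **Nothing is stated wrongly.** A Bonferroni split is standard and matches its stated purpose, and a fuller plan not shown here might contain a testing sequence. This stands, and it is why the point is a suggestion only. The article does, however, fix a level for each variable and give the reason, so the suggestion addresses a stated rule.

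**The split is not protection for nothing.** A reader might infer that a step-down rule with a 5% second step costs no error control. The plan also names dose-pair comparisons. With these counted, the error in the critical case goes from about 3.2% to about 5.6%. The slack in the present split covers the pairs, so the 4.17% version is the one to recommend, with its smaller gain.

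**The gain is mostly on an overall test.** A significant three-group F-test shows that some group differs. It does not show that equol lowers BP at a given dose, or that the higher dose does more. This stands: most of the added successes would come without a significant dose-versus-placebo pair.

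**Showing both is a chosen yardstick.** The trial is sized on SBP alone, and nothing requires both variables to succeed. This also stands.

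**Sample size.** A reader might take the step-down rule as a remedy for sizing at 5% while testing at 2.5%. It is not. Two-group power for 5 mmHg at 2.5% is Φ(2.806 − 2.241) = 71% with 63 per group (76% with 69), and the first step stays at 2.5%.

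**Conclusion.** The point holds as an optional gain in efficiency. The current split validly controls 5% for the two overall BP tests, and the documents do not support reading it as an error or as inflated. A step-down rule with the same first step never rejects less on these tests.

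With the dose pairs inside the 5%, the gain is about 7–8 points in the chance of showing both variables. With a 5% second step it is about 9–11 points at 63 per arm, and that version is valid only if the 5% is declared to cover the two overall tests alone.

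That the step-down rule never rejects less does not depend on the assumptions. The size of the gain does: it rests on the assumed DBP effects, DBP SD and correlation. Over a wider grid (correlation 0–0.9, 63 or 69 per arm, DBP effect 0.6–1.0 times the SBP effect in SD units), the gain with a 5% second step ranged from 6.6 to 12.8 points.

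**What to change.** In the Statistical analysis section, replace the fixed split with wording such as:

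> The smaller of the two primary ANOVA p-values (24 h mean SBP, 24 h mean DBP) is tested at 2.5%. If it is significant, the other is tested at 4.17%. Bonferroni dose pairs are examined only after a significant overall test on that variable, at 0.83% each.

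If the 5% is meant for the two overall tests only, say so explicitly; the second step may then be 5%. The levels for the secondary and tertiary outcomes are untouched.

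The cost is a few lines of wording, settled before unblinding, with no added data or participants. The price in error is that slack in the present rule is used up: in the critical case the error rises from about 3.2% to about 4.8%, still within 5%. Any report should make clear that a second variable significant on the overall test alone does not show which dose works.

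### Stratified analysis is named as the way to judge whether effects differ between subgroups, with no direct comparison between strata; a treatment-by-subgroup interaction term would answer the question

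*Protocol article*

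**What the plan says.** The subgroup plan is one sentence at the end of the Statistical analysis section of the protocol article: "Further stratification analysis will be conducted to examine if the effects differed across subgroups such as years since menopause and BMI etc". It gives no interaction or homogeneity test, no cut-points, no significance level and no closed list of factors.

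The same section is specific about its other analyses. It states "The major approach of analysis will be one way analysis of variance (ANOVA", and it names analysis of covariance, a trend test for dose and Bonferroni post hoc comparisons. Each of the two primary ambulatory pressures "will be tested at a significance level of 2.5 % in order to maintain an overall 5 % level".

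The figures needed to size the point are in Sample size planning. The assumed effect is given as "Assuming a reduction of 5 mmHg of treatment effect on SBP (main effect". The variability comes from an earlier trial that "showed a 4.2 mmHg net reduction (SD of change 10 mmHg) in SBP". The plan then says "63 subjects per group will yield a power of at least 80" %, "at 5 % level of significance (for a 2-side t-test", and that "69 subjects per group and a total 207 subjects (63 × 3 × 110 %) will be recruited".

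**The concern.** Whether an effect differs between two groups of women is a question about the difference between two treatment effects. Analysing each stratum separately gives two effects, each set against zero, and leaves the comparison to the reader. Each stratum holds only part of the sample, so its power is well below that of the whole trial. One stratum can easily reach significance while the other does not, although the true effect is the same in both.

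At stake is a statement that equol lowers pressure in, say, leaner or more recently menopausal women only, when nothing differs. The article presents the trial as a basis for public health provision of equol, so a spurious restriction of that kind would matter for the message. It would not alter the primary comparison.

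**Working it through.** **Inputs.** From Sample size planning: effect 5 mmHg, SD of change 10 mmHg, 63 evaluable and 69 recruited per arm, two-sided 5%. From Statistical analysis: 2.5% for each primary pressure, and Bonferroni for three pairs. My assumptions: one factor, two equal strata (31.5 per arm per stratum if 63 are analysed, 34.5 if 69 are), the same true effect in both, and an apparent difference meaning significance in exactly one stratum.

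**The plan's own figure.** n = 2 × (1.960 + 0.842)² × 10² / 5² = 62.8, so 63 per arm. The normal approximation gives power 0.801 (0.795 with the t distribution). 63 × 3 × 1.10 = 207.9, stated as 207. The plan's figure is reproduced.

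**Power in one stratum, high dose versus placebo.** The standard error is 10 × √(2/31.5) = 2.52 mmHg, and 5/2.52 = 1.984.

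- At 5%: Φ(1.984 − 1.960) = 0.510 (t: 0.497).
- At 2.5%: Φ(1.984 − 2.241) = 0.399 (t: 0.383).

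**Chance that exactly one stratum is significant.** The strata are independent, so this is 2p(1 − p).

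- At 5%: 2 × 0.497 × 0.503 = 0.50.
- At 2.5%: 2 × 0.383 × 0.617 = 0.473 (normal approximation 0.479).

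The ranges below run over 63 to 69 women per arm and over the normal and t calculations.

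| Uniform true effect | 5% level | 2.5% level | Bonferroni pair, 2.5%/3 |
|---|---|---|---|
| 5 mmHg | 0.50 | 0.47–0.49 | 0.36–0.41 |
| 4.2 mmHg (earlier trial) | 0.47–0.48 | 0.40–0.43 | 0.26–0.30 |
| 2.5 mmHg | 0.28–0.29 | 0.18–0.20 | 0.09–0.10 |
| None | 0.095 | 0.049 | 0.017 |

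The last row is 2 × 0.05 × 0.95 = 0.095 and 2 × 0.025 × 0.975 = 0.049, and likewise for 2.5%/3.

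**Variations at 5 mmHg.**

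- Three-group ANOVA within each stratum: 0.48–0.50 at 5% and 0.41–0.49 at 2.5%, depending on the mean in the low-dose arm.
- Unequal splits from 40:60 to 20:80, 63 per arm, 5% level: 0.51–0.61.
- Two unrelated factors, at least one discordant result (20,000 simulated trials): 0.67 at 5% and 0.64 at 2.5%.

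**Interaction test for comparison.** In the same simulations it declared a false difference in 4.6–5.2% of trials at the 5% level and 2.4–2.5% at the 2.5% level, whatever the common effect. With two factors, at least one false difference arose in about 9–10% and 5%.

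**Power of the interaction test.** The standard error is 10 × √(4/31.5) = 3.56 mmHg. For a true 5 mmHg difference between halves, Φ(5/3.56 − 1.96) = 0.29 (0.31 with 69 per arm). For 80% power the difference must be (1.960 + 0.842) × 3.56 = 9.98 mmHg (9.54 with 69 per arm).

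**The case against.** The strongest reply is that the article does not prescribe the error. It does not say that a test will be run in each stratum, or that a difference will be declared when one stratum is significant and the other is not. Stratified estimates can be compared by a homogeneity test or shown with intervals, and a full analysis plan, not shown here, may say so. A reader might infer that following the sentence as written leads to a false subgroup finding in half of all trials. The article does not support that: the reading rule is an assumption, and the rate depends on the true effect. No effect at all is also a uniform effect, and then the rate is only 5–10%.

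This part of the objection stands, and so does a point about the SD. The 10 mmHg comes from an earlier trial, and the article itself credits ambulatory measurement with better precision. If the SD were 7 mmHg (an assumption), with 63 per arm, power per stratum would be about 0.80 at 5% and discordance 2 × 0.80 × 0.20 = 0.32. At 2.5% the figures would be about 0.70 and 0.42.

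It is also fair that this is a further analysis, placed after the primary, secondary and tertiary tests, and that details of subgroup work are often left to an analysis plan.

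What does not stand is that this is only an omission. The sentence pairs a stated question with a stated method, in a section that names its other tests one by one, and that method alone does not answer the question.

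**Conclusion.** The point holds as a criticism of method. Stratified analysis is the only tool named for deciding whether effects differ, and separate stratum results do not test a difference.

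The size is conditional. With one factor in two equal strata, SD 10 mmHg, a uniform effect near the planned 5 mmHg, and a difference read as significance in one stratum only, about half of trials would show discordant strata at 5%. At the 2.5% level used for the primary outcomes it is slightly under half. The rate is lower for a smaller uniform effect, for Bonferroni pairs or for a smaller SD, and higher for unequal strata or several factors. An interaction test holds its nominal level for each factor under all common effects examined.

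Severity is low: the primary comparison, the sample size and the division of the significance level are not affected.

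**What to change.** Replace the sentence with one along these lines: effect modification by years since menopause, BMI and any other listed factor will be assessed by a treatment-by-subgroup interaction term, reported as an estimate with its confidence interval and labelled exploratory; estimates within strata will be shown with intervals for description only.

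Keeping years since menopause and BMI continuous is optional. It avoids choosing cut-points but assumes a form for the relation. Adding baseline adjustment is a separate modelling choice and is not needed for this change.

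The cost is one sentence and one model term per factor. The drawback is low power, as shown above, so most interaction results will be inconclusive. They should be reported through the interval and not read as evidence that effects are equal. The nominal error also applies to each factor separately, which is a reason to close the open-ended list and keep the exploratory label.

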## Results

The proposed study flow chart is indicated in Fig. 1. Baseline characteristics of 292 pre-hypertensive postmenopausal women who were non-equol producers were listed in Table 1.

**Fig. 1 Fig1:**
[figure not shown]
Study flow chart of the proposal

**Table 1 Tab1:** Baseline characteristics among 292 non-equol producing postmenopausal women with prehypertension

	Non-Equol producers
n	292
Age (y)	57.6 ± 4.6
Menopausal years (y)	8.2 ± 5.3
Age at menarche(y)	13.2 ± 1.8
Ever use of contraceptives (%)	126 (50.6)
Ever use of HRT (%)	38 (15.3)
Dietary intake (from FFQ)	
Energy (kcal/d)	2100.7 ± 1018.6
Protein (g/1000 kcal)	55.8 ± 13.2
Total fat (g/1000 kcal)	21.2 ± 6.9
Fiber (g/1000 kcal)	21.0 ± 8.8
Cholesterol (mg/1000 kcal)	146.2 ± 90.1
Isoflavones (mg/1000 kcal)	7.03 ± 7.83
Total PA (MET-min/d)	1445.6 ± 728.2
Occupational PA	586.1 ± 759.5
Housework PA	558.7 ± 459.9
Sports PA	141.0 ± 166.2
Habitual tea drinking (%)	195 (78.6)
Habitual alcohol drinking (%)	18 (7.3)
Habitual coffee drinking (%)	84 (33.9)
Passive smoking (%)	43 (17.4)
Anthropometrics measures, BP and lipids	
Body weight (kg)	55.7 ± 9.0
BMI (kg/m^2^)	23.0 ± 3.2
WHR	0.838 ± 0.050
SBP (mmHg)	135.1 ± 16.6
DBP (mmHg)	83.1 ± 9.6
TG (mmol/L)	1.41 ± 0.79
TC (mmol/L)	5.76 ± 0.90
Hs-CRP (mg/L)	1.90 ± 2.08

Data are presented as mean ± standard deviation for continuous variables or number (%) for categorical variables. FFQ indicates food frequency questionnaires; PA indicates physical activity; Habitual drinking means drinking alcohol, tea or coffee more than 1 time per week; METs are multiples of resting metabolic rates and a MET-minute is computed by multiplying the MET score of an activity by the minutes performed. Dietary nutrients intakes were calculated mainly based on the China Food Composition Table 2002 and 2004. *SBP* systolic blood pressure, *DBP* diastolic blood pressure, *TG* triglycerides, *BMI* body mass index, *WHR* waist to hip ratio, *Hs-CRP* high sensitivity c-reactive protein

## Discussion

The results of this RCT will produce direct evidence on the effectiveness of natural S-equol on BP and vascular function among equol non-producing Chinese postmenopausal women with pre-hypertension or early untreated hypertension. To our knowledge, this will be the first RCT specifically conducted among non-equol producers to test the effectiveness of S-equol supplementation on BP and vascular function, and also provide evidence for the optimal dosage of equol. S-equol is natural supplement derived from soy germ by fermentation. The proposed level of intake has been used in several clinical trials. No severe adverse effects have been observed in human studies.

This randomized, double-blind, placebo-controlled trial will be performed in community subjects with prehypertension or early untreated hypertension. If the antihypertensive effect of natural S-equol is proven, the provision of natural equol to those high risk adults who are unable to produce equol due to a lack of intestinal equol-producing bacteria or some other factors, could have enormous public health implications for the primary and secondary prevention of hypertension and cardiovascular diseases on a population basis. These research efforts may provide alternative remedy to improve cardiovascular health, and also have significant implications for industry in the provision of suitable soy products or supplementation for the prevention of hypertension and its related complications. With the high prevalence of hypertension in postmenopausal women, this study on the hypotensive effect of equol will explore an area with important public health implications both locally and internationally.

### Ethics approval

The study ethics was approved by the Ethics committee of the Chinese University of Hong Kong (CREC Ref. No.: CRE-2013.119-T)

## Abbreviations

ABPM: ambulatory BP monitor
ANOVA: one way analysis of variance
BMI: body mass index
BP: blood pressure
CHD: coronary heart disease
CRP: C-reactive protein
CVD: cardiovascular diseases
EF: endothelial function
ET-1: endothelin-1
FMD: flow mediated dilation
HPLC: high performance liquid chromatography
ICAM-1: soluble intercellular adhesion molecule–1
PWA: pulse wave analysis
RCT: randomized controlled trial
VCAM-1: soluble vascular cell adhesion molecule–1
WHR: waist to hip ratio
